## 2.4 Potential Risks and Benefits

### 2.4.1 Potential Risks

Potential physical risks include:

- fatigue due to answering study questionnaires
- pain and discomfort during the physical exam

The medical risks of participating in this study are those inherent to assigned treatments which are standards of care.

- For **physical therapy**, the risks include increased pain or no improvement of pain and function, and adhesive capsulitis (frozen shoulder).
- For **surgery**, the risks include those commonly associated with surgery, such as: post-operative bleeding or infection, blood clot, hospital readmission, complications related to anesthesia, and, in rare cases, death. Other risks for surgical treatment of rotator cuff tear include: nerve injury, adhesive capsulitis (frozen shoulder), and no improvement of pain & function.

**MRI Risks:** There are no known major risks associated with an MRI scan. But, it is possible that harmful effects could be discovered in the future. Known risks

include claustrophobia, nausea, dizziness, flashing lights in eyes, and metallic taste.

In addition, there may be risks associated with the study that are unknown or unexpected.

#### **2.4.2 Potential Benefits**

There are no direct benefits to subjects participating in the study. Knowledge gained about the effectiveness of surgery versus non-operative treatments may benefit future patients and providers.

### **3 OBJECTIVES**

#### **3.1 Study Objectives**

**Aim 1:** To compare pain and function in patients undergoing operative versus non-operative treatment of atraumatic rotator cuff tears at 12 months of follow-up.

**Aim 2:** To assess effects of rotator cuff tear size and age on comparative outcomes (measured by SPADI) in operative versus non-operative treatments for atraumatic rotator cuff tears.

#### **3.2 Study Outcome Measures**

Patients with rotator cuff tear present with shoulder pain and loss of function. Hence, our outcomes are patient-reported measures of pain and function.

##### **3.2.1 Primary Outcome**

The primary outcome measure for this study is the difference between baseline and 12 month SPADI.

##### **3.2.2 Secondary Outcome**

ASES will be used as a secondary outcome.

## **4 STUDY DESIGN**

### **4.1 Primary Study**

This is an unblinded, multi-center, pragmatic randomized controlled clinical trial of operative versus non-operative treatments for atraumatic rotator cuff tears. A sample size of 700 patients will be enrolled with approximately equal numbers of patients randomized to operative treatment (surgery + post-op physical therapy) and non-operative treatment (physical therapy only without surgery). Both treatments are current standards of care. The duration of enrollment is expected to last approximately 3.5 years. For the main study and analysis, a 12-month follow-up is needed, with the duration of the primary study lasting for approximately 5 years.

Upon enrollment at baseline, patients will fill out study questionnaires, undergo a brief physical examination, and, if applicable, have a research MRI. Follow-up for the primary study will be performed via questionnaires at 3, 6, and 12 months.

### **4.2 Sub-study**

A sub-study will follow subjects after the primary end point of one (1) year for the trial has been met. The sub-study will follow subjects via questionnaires at yearly intervals for up to 10 years (i.e., for 9 years after the primary end point). The sub-study may also include a physical examination and research MRI at 2-7 years interval from enrollment. The objective of the sub-study is to assess longer-term patient-reported outcomes of operative and non-operative treatments (measured by SPADI and ASES) in patients with rotator cuff tears. It will also assess whether structural changes such as tear size and fatty infiltration of the rotator cuff muscle are different in the operative and non-operative groups.

## 5 STUDY ENROLLMENT AND WITHDRAWAL

|                               |                                                              |
|-------------------------------|--------------------------------------------------------------|
| Target Sample Size:    | 700 participants                                             |
| Gender:                | Both genders                                                 |
| Age:                   | ≥50 years to <85 years                                       |
| Demographic Group:     | All demographic groups included                              |
| General Health Status: | Patients with shoulder pain and atraumatic rotator cuff tear |

### Screening to achieve 700 participants:

- Expected number pre-screened: 175,000 (250 for every 80 evaluable patients)
- Expected number screened in clinic: 56,000 (80 for every 8 eligible)
- Expected number eligible for study: 5,600 (8 for every 1 recruited)

### 5.1 Subject Inclusion Criteria

In order to be eligible to participate in this study, an individual must meet all of the following criteria:

- Aged ≥50 years to <85 years
- Shoulder pain and/or loss of active motion, strength or function
- MRI-confirmed partial- or full-thickness supraspinatus and/or infraspinatus tear of 4cm or less in longitudinal dimension
- Medically fit for surgery, defined as Category I-III per American Society of Anesthesiologists (ASA) Physical Status Classification (see Table 1: ASA Physical Status Classifications and Examples)
- Ability and willingness to provide informed consent

**TABLE 1. ASA Physical Status Classifications and Examples**

| ASA Physical Status Classification | Definition                                                        | Examples                                                                                                                                                                                                                                                                                                                                                                                                                              |
|-------------------------------------------|--------------------------------------------------------------------------|----------------------------------------------------------------------------------------------------------------------------------------------------------------------------------------------------------------------------------------------------------------------------------------------------------------------------------------------------------------------------------------------------------------------------------------------|
| ASA I                              | A normal healthy patient                                                 | Healthy, nonsmoking, no or minimal alcohol use                                                                                                                                                                                                                                                                                                                                                                                               |
| ASA II                             | A patient with mild systemic disease                                     | Mild diseases only without substantive functional limitations. Examples include (but not limited to): current smoker, social alcohol drinker, pregnancy, obesity ( $30 < \text{BMI} < 40$ ), well-controlled DM/HTN, mild lung disease                                                                                                                                                                                                       |
| ASA III                            | A patient with severe systemic disease                                   | Substantive functional limitations; one or more moderate to severe diseases. Examples include (but not limited to): poorly controlled DM or HTN, COPD, morbid obesity ( $\text{BMI} \geq 40$ ), active hepatitis, alcohol dependence or abuse, implanted pacemaker, moderate reduction of ejection fraction, ESRD undergoing regularly scheduled dialysis, premature infant PCA $< 60$ wk, history ( $> 3$ mo) of MI, CVA, TIA or CAD/stents |
| ASA IV                             | A patient with severe systemic disease that is a constant threat to life | Examples include (but not limited to): recent ( $< 3$ mo) MI, CVA, TIA or CAD/stents; ongoing cardiac ischemia or severe valve dysfunction; severe reduction of ejection fraction; sepsis; DIC; ARD; or ESRD not undergoing regularly scheduled dialysis                                                                                                                                                                                     |
| ASA V                              | A moribund patient who is not expected to survive without the operation  | Examples include (but not limited to): ruptured abdominal/thoracic aneurysm, massive trauma, intracranial bleed with mass effect, ischemic bowel in the face of significant cardiac pathology or multiple organ/system dysfunction                                                                                                                                                                                                           |

| ASA Physical Status Classification                                                                                                                                                                                                                                                                                                                                                                                                                                                                                                                    | Definition                                                                      | Examples |
|-------------------------------------------------------------------------------------------------------------------------------------------------------------------------------------------------------------------------------------------------------------------------------------------------------------------------------------------------------------------------------------------------------------------------------------------------------------------------------------------------------------------------------------------------------|---------------------------------------------------------------------------------|----------|
| ASA VI                                                                                                                                                                                                                                                                                                                                                                                                                                                                                                                                         | A declared brain-dead patient whose organs are being removed for donor purposes |          |
| ARD , acid reflux disease; ASA , American Society of Anesthesiologists; BMI , body mass index; CAD , coronary artery disease; COPD , chronic obstructive pulmonary disease; CVA , cerebral vascular accident; DIC , disseminated intravascular coagulation; DM , diabetes mellitus; ESRD , end-stage renal disease; HTN , hypertension; MI , myocardial infarction; PCA , postconceptual age; PS , physical status; TIA , transient ischemic attack |                                                                                 |          |

## 5.2 Subject Exclusion Criteria

Any individual who meets any of the following criteria will be excluded from participation in this study:

- Primary diagnosis is something other than a rotator cuff tear
- History (in last 2 years) of shoulder fracture involving the humeral head on affected side
- Previous rotator cuff surgery on affected side
- Isolated subscapularis &/or teres minor tear on affected side
- Acute rotator cuff tear caused by a severe trauma (see TABLE 2: Trauma Classification)
- Shoulder used as a weight-bearing joint
- Contraindication to MRI (claustrophobia, pacemaker, pregnancy, shoulder implant, etc.)
- Glenohumeral osteoarthritis on xrays/MRI, as determined by recruiting MD
- Grade 4 fatty infiltration of rotator cuff (any tendons)

- Candidate for reverse shoulder arthroplasty or total shoulder arthroplasty at baseline
- Non-English speaking (questionnaires only validated in English)
- Severe problems with maintaining follow-up expected (such as but not limited to history of substance abuse, homelessness/incarceration, dementia, brain injury, and psychotic disorders)

Patients receiving workers' compensation are not excluded from the trial.

**TABLE 2: Trauma Classification (adapted from Mackay, et. al., 2007)**

| Low Velocity Trauma                                                                                          | Severe Trauma                                                                                                                         |
|--------------------------------------------------------------------------------------------------------------|---------------------------------------------------------------------------------------------------------------------------------------|
| Falls from standing height or less                                                                           | Falls from greater than standing height (e.g., falls while standing on a ladder, chair, porch, table, steps, or other raised surface) |
| Minimal trauma other than a fall (e.g., turning over in bed)                                                 | Motor vehicle crashes                                                                                                                 |
| Moderate trauma other than a fall (e.g., collisions with objects or another person during normal activities) | Struck by vehicle or other fast-moving projectile (e.g., bullet, baseball, etc.)                                                      |
|                                                                                                              | Assault (i.e., injuries intentionally inflicted by another person)                                                                    |

### 5.3 Strategies for Recruitment and Retention

Study participants will be recruited through the clinics of designated recruiting physicians at each site. Potential recruits may be identified through other mechanisms (e.g. primary care provider or non-operative provider referral, patient self-referral after hearing about the study, advertising, etc.) and referred to the clinics of recruiting

physicians for evaluation. Patients in these clinics will be screened to determine eligibility and, if eligible, approached for enrollment in the study. Patients may also be contacted prior to their clinic visit to make them aware of the study.

### **5.3.1 Recruitment / Consent Videos**

Patients will typically be shown two short, standardized videos:

- 1) Recruitment Video – This video provides information about the trial (purpose and design), what is involved (length and procedures), and participant compensation.
- 2) Consent Video – This video provides information about risks and benefits, withdrawal/removal from the study, and information that will be collected.

Use of these videos can help ensure consistency of information presented to study candidates across all sites. The recruitment video has been designed to educate participants about the purpose of the trial and what it involves as well as the importance of randomized assignment and following through with their assigned treatment for 6 months.

The RAs and recruiting MD will also introduce the study to the patient via sample standardized scripts and be available to answer questions that the patient may have. In the event that the patient does not wish to watch the videos but wants to participate in the study, the RA may substitute a verbal discussion of the content using the video scripts as a guide.

### **5.3.2 Crossover**

Subjects may cross over from one treatment to another at any point during the trial. Crossovers are usually from the non-operative to the operative arm (although a few patients randomized to the operative arm may not have surgery and have only physical therapy). It takes about 6 months for non-operative physical therapy to be effective. Hence, at the time of recruitment, subjects will be encouraged to stay in their randomized treatment arm for at least 6 months. However, subjects may cross over at any time point if they choose to do so and will still remain in the study.

If a subject crosses over within 6 months following randomization, or does not pursue either treatment within 12 months after randomization, it will be considered a protocol deviation.

### **5.3.3 Compensation**

Subjects will be compensated for the time and inconvenience of participating in the study. They will be paid:

- \$100 for the baseline enrollment visit,
- \$50 for each follow-up questionnaire completed (at 3mo, 6mo, 12mo for the main study, and annually in years 2-10 for the sub-study), and
- \$100 for a return visit & MRI for the sub-study (once, approximately 2-7 years after treatment for the sub-study).
- Subjects who undergo a screening MRI at baseline for research purposes will be paid \$100 for the MRI visit.

In a subset of patients, a research MRI to determine eligibility for the study may be offered to the subject as determined by the recruiting physician. Those subjects who receive a screening MRI for research purposes will be paid \$100 for the time and inconvenience of returning for the screening MRI.

| Main Study                    |                 |      |      |       |  | Sub-Study |      |      |      |      |      |      |      |       |                    |
|-------------------------------|-----------------|------|------|-------|--|-----------|------|------|------|------|------|------|------|-------|--------------------|
| Screening MRI (if applicable) | Base-line Visit | 3 Mo | 6 Mo | 12 Mo |  | 2 Yr      | 3 Yr | 4 Yr | 5 Yr | 6 Yr | 7 Yr | 8 Yr | 9 Yr | 10 Yr | Return Visit & MRI |
| \$100                         | \$ 100          | \$50 | \$50 | \$50  |  | \$50      | \$50 | \$50 | \$50 | \$50 | \$50 | \$50 | \$50 | \$50  | \$100              |

### 5.3.4 Long-term Participation Strategies

Several strategies will be used to promote continued participation.

- **Complete Contact Information** - Both primary and secondary addresses, phone numbers, and emails will be collected for subjects at baseline as well as on all follow-up questionnaires. If subjects live at an alternate address for part of the year, it will be noted which months are spent at each address.
- **Multiple Means of Contact** – Subjects will be contacted by phone, email, mail, or text as needed. Subjects can specify their preferred means of contact. Alternate means of contact may be used if initial attempts to reach the subject via their preferred means are unsuccessful.
- **Secondary Contact Person** – The name, relationship, address, phone, and email of a secondary contact person will be collected at baseline as well as on all follow-up questionnaires. This person will be contacted if all other attempts to reach the subject fail.

- **Option of Paper or Electronic Questionnaires** – Subjects may choose to complete follow-up questionnaires either on paper or electronically (via tablet or computer) per their preference.
- **Follow-Up Reminders & PI calls** – Subjects who do not complete/return follow-up questionnaires within the expected timeframe will receive follow up reminders. If questionnaires are not completed/returned after at least three reminders by study personnel, subjects may receive a call from the study PI or site PI.

### **5.3.5 Sharing Results with Participants**

Results of the study will be made available on the study website:  
[www.shoulderstudy.org/studies/arc-trial](http://www.shoulderstudy.org/studies/arc-trial).

## **5.4 Treatment Assignment Procedures**

Enrolled participants will be assigned to treatment with approximately equal numbers of subjects randomized to operative and non-operative treatment. Subjects will be randomized ONLY after eligibility has been confirmed and informed consent has been obtained.

Randomization will be automatically assigned within REDCap after strata information has been entered. Randomization is initiated manually by study personnel. The database has been programmed so that randomization is only possible if all necessary information has been entered and all eligibility criteria have been documented as met.

### **5.4.1 Randomization Procedures**

Randomization will be stratified by site, age class (< 65 years; ≥ 65 years), and tear size class (> 0 < 2 cm; ≥ 2 ≤ 4 cm) and blocked within strata using a random sequence of differing block sizes (i.e., 2, 4 and 6). Accordingly, the maximum treatment assignment imbalance at any site is 3 participants. Randomization strings for each site will be unique, randomly generated, and administered in real time using a randomization module within REDCap.

The study principal investigator, trial coordinator, and site investigator will receive automatically generated emails when a participant is randomized.

Randomization assignments will be accessible 24 hours a day, 7 days a week via REDCap. If REDCap is unavailable locally for any reason, site personnel will call the study coordinator at the coordinating center to complete randomization. If REDCap

is down globally, randomization will not take place until the system is back up, or the subject affected will not be randomized.

Additional placeholder sites have been included in the randomization table, so that new sites or replacement sites may easily be added to the randomization module in REDCap (if needed) once the study is under way.

#### **5.4.2 Masking Procedures**

Intervention arms will not be masked, as this is a non-blinded study.

### **5.5 Subject Withdrawal**

Subjects may withdraw from the study voluntarily or be terminated by the principal investigator.

#### **5.5.1 Reasons for Withdrawal**

Subjects are free to withdraw from participation in the study at any time upon request.

An investigator may terminate a subject's participation in the study if:

- Any serious adverse event (SAE) or other medical condition or situation occurs such that the subject cannot continue or continued participation in the study would not be in the best interest of the subject.
- The subject is deceased.
- The subject does not complete any follow-up questionnaires in the first year.
- The subject does not complete annual follow-up questionnaires two years in a row for the sub-study.
- The study ends earlier than anticipated.

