#### **5.5.2 Handling of Subject Withdrawals or Subject Discontinuation of Study Intervention**

Subjects who are withdrawn from the study, either through voluntary discontinuation, for failure to complete study questionnaires, or by decision of the principal investigator for reasons enumerated above, will be recorded as terminated. They will be sent a letter confirming their early termination from the study and will no longer be

followed. They will not be sent any further follow-up questionnaires or brought back for a follow-up visit & MRI (if applicable).

If a subject is withdrawn due to an SAE or other medical condition that precludes their continuation in the study, the study or site PI will call the subject to discuss and ensure appropriate medical treatment or follow up is arranged.

The study sample size has been calculated to allow for attrition due to early withdrawal or discontinuation.

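### Two missed annual questionnaires can end a sub-study subject's follow-up for good, turning intermittent non-response into permanent loss for the long-term objectives

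*Protocol*

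**What the plan says.** Section 4.2 sets the long-term aims. For patient-reported outcomes, "The sub-study will follow subjects via questionnaires at yearly intervals for up to 10 years". For structure, "The sub-study may also include a physical examination and research MRI at 2-7 years interval from enrollment", and "It will also assess whether structural changes such as tear size and fatty infiltration of the rotator cuff muscle are different" between the two arms. Section 12.5 says the sub-study will be analysed much as Aims 1 and 2, with more time points.

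Section 5.5.1 opens its list of grounds with "An investigator may terminate a subject's participation in the study if". Two of the grounds are non-response alone: "The subject does not complete any follow-up questionnaires in the first year" and "The subject does not complete annual follow-up questionnaires two years in a row for the sub-study".

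Section 5.5.2 treats this route as distinct from voluntary discontinuation. Subjects withdrawn "for failure to complete study questionnaires, or by decision of the principal investigator for reasons enumerated above, will be recorded as terminated". They receive a termination letter and are no longer followed: "They will not be sent any further follow-up questionnaires or brought back for a follow-up visit & MRI (if applicable"). Nothing in either section says how such a subject could be taken back into follow-up.

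**The concern.** A missed form and a withdrawal from the study are different events. Someone who skips two annual questionnaires has withdrawn nothing and may answer the next one, or may attend an MRI visit, which needs no questionnaire at all. Once terminated, that person is never asked again. Because the data are never requested, no later analysis can recover them.

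The late time points and the MRI comparison are at stake. The loss accumulates over nine annual questionnaires and leaves the later years to the most persistent responders. Treatment is unmasked (section 5.4.2), so response could depend on how the shoulder is doing or on satisfaction with the assignment. Section 5.5.1 also gives no criteria for using the non-response grounds, so sites could apply them differently.

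The ground also sits awkwardly beside the rest of the protocol. Section 6.5.4 keeps a subject in follow-up even when the MRI review finds no tear or one larger than 4 cm. Section 5.3.2 keeps crossovers in the study. Section 5.3.4 sets out several measures to keep people participating over the long term.

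**Working it through.** The protocol states no figure for this loss, so there is none to reproduce. What follows is the text check and then an illustration on stated assumptions.

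**What one use of the option removes.** Annual questionnaires run over years 2 to 10, which is 9. The earliest trigger is missing years 2 and 3. Termination then removes years 4 to 10, which is 7 of 9. It also removes the MRI if that has not been done, with up to 7 − 3 = 4 years of its window left.

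**Assumptions for the illustration.** Annual non-response q is not given in the protocol; 10%, 20% and 30% are assumed. The option is used every time its condition is met. All 700 subjects enter the sub-study.

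**Independent misses.** Let a(n) be the probability of no two consecutive misses in n annual questionnaires:

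a(n) = (1 − q)·a(n−1) + q(1 − q)·a(n−2), with a(0) = a(1) = 1.

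- Terminated by year 10: 1 − a(9).
- Able to answer at year 10 but never asked: 1 − a(8). Termination must come from years 2 to 9, and under independence that does not depend on the year-10 answer.
- Terminated by year 6, while the MRI window is still open: 1 − a(5).

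For q = 0.20 the sequence from a(2) is 0.960, 0.928, 0.896, 0.865, 0.836, 0.807, 0.779, 0.752. Hence 1 − a(9) = 0.248, 1 − a(8) = 0.221 and 1 − a(5) = 0.135. Answers that would have been given but are never requested were counted over all 2⁹ = 512 response patterns.

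| Independent misses | q = 10% | q = 20% | q = 30% |
|---|---|---|---|
| Terminated by year 10 | 7.2% | 24.8% | 46.4% |
| The same, of 700 | 50 | 173 | 325 |
| Year-10 responders never asked | 6.3% | 22.1% | 42.2% |
| Answers never requested, per 700 | 162 | 520 | 910 |
| Share of all obtainable answers lost | 2.9% | 10.3% | 20.6% |
| Terminated by year 6 | 3.7% | 13.5% | 27.3% |

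At q = 5% the share of year-10 responders never asked is 1.7%.

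**Clustered misses.** Independence treats someone who has just missed two years as no less likely to answer than anyone else. To relax this, each subject gets a personal miss rate from a beta distribution with mean q and within-subject correlation ρ, so that α = q(1/ρ − 1) and β = (1 − q)(1/ρ − 1). A pattern with s misses in 9 has probability B(α + s, β + 9 − s) / B(α, β). The same 512 patterns were summed with ρ, also an assumption, from 0.2 to 0.7.

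| Clustered misses, ρ from 0.2 to 0.7 | q = 10% | q = 20% | q = 30% |
|---|---|---|---|
| Year-10 responders never asked | 8% to 4% | 19% to 7% | 31% to 11% |
| Share of all obtainable answers lost | 4% to 2% | 10% to 4% | 17% to 6% |

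Clustering shrinks the loss at 20% and 30%. At 10%, moderate clustering raises it slightly (8.2% at ρ = 0.2, against 6.3% under independence). The loss does not vanish at any setting tried.

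**The case against.** The strongest reply is that the wording is permissive. Section 5.5.1 gives the investigator an option, and section 5.5.2 acts only on subjects who have actually been withdrawn. A reader might infer that two missed forms trigger termination automatically. The text does not say so, and the figures above are therefore what happens if the option is always taken. This limits the size of the point but does not remove it, because no criteria confine the option.

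Second, a two-year non-responder may already have been through the section 5.3.4 reminders and principal investigator calls twice, so stopping contact is a recognisable choice about burden. That is fair, and the yield per further contact will be low. It does not explain why an outstanding MRI invitation must lapse too.

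Third, the MRI loss is easily overstated. The MRI is optional and done once, so it is lost only if planned and still outstanding. The year-6 row above is an upper limit on subjects exposed, not a count of MRIs lost.

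Fourth, a reader might infer that the arms would be compared with bias. Nothing in the protocol shows that non-response, or use of the option, differs by arm. The longitudinal mixed model of section 12.2.1 can use a terminated subject's earlier scores, and missing-data sensitivity analyses are planned. Bias arises only where the added missingness is informative given those scores. The certain cost is precision.

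One defence fails. Section 5.5.2 says the sample size allows for attrition, but the power figures in section 12.3 concern 12-month SPADI change only. No sub-study sample size is stated.

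**Conclusion.** The point holds in limited form. The protocol permits, but does not require, permanent termination of consenting sub-study subjects for non-response alone. Where the permission is used, their later questionnaires and any outstanding MRI are lost to the section 4.2 objectives. With the option always used and annual non-response of 10% to 30%, about 6% to 42% of those able to answer at year 10 would never be asked under independence, and roughly 4% to 31% under clustering. The non-response rates, the clustering and full use of the option are all assumptions, so these are illustrations and not forecasts.

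The two-missed-years ground begins after year 1 and leaves the 12-month primary endpoint and its power alone; no threat to the primary result should be read into it. The separate year-1 ground was not modelled. The matter deserves correction because it cannot be repaired at analysis and costs little to change now.

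**What to change.** Amend two sections.

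- In 5.5.1, delete the ground based on two consecutive missed annual questionnaires. For consistency, also delete the ground based on returning no questionnaire in year 1.
- In 5.5.2, delete the clause that makes failure to return questionnaires a route to being recorded as terminated.
- State that a missed time point is recorded as missed. Subjects whose only issue is non-response keep receiving each scheduled questionnaire, and the MRI invitation if the MRI has not been done.

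Leave every other ground in 5.5.1 as it stands, including the one for serious adverse events and the subject's best interest. An instruction to contact everyone who has not died or withdrawn consent would override that ground and goes further than this point requires.

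The cost is a short amendment and a little more mailing and reminder work with a low yield per contact. The $50 payment in section 5.3.3 falls due only for questionnaires that are completed; an MRI visit that takes place would bring its own $100.
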